#### Study population

2.2.3

Patients with T2DM attending the outpatient of Endocrinology and Metabolism Clinical Sciences Institute of Tehran University of Medical Sciences in Tehran will be invited to the study. The patients will be diagnosed by an endocrinologist and by their medical records, using the American Diabetic Association, fasting blood sugar ≥126 mg/dL or 2 hours postparandial ≥200 mg/dL, or HbA1C ≥6.5%.^[29]^ Patients should meet the eligibility criteria. After their identification, the patients will be referred to the investigator to be enrolled in the study and to be explained about the goals, methods, and benefits of the intervention. Written informed consent will be obtained prior to the recruitment. The general questionnaire, 24-hour dietary recall questionnaire, short-form International Physical Activity Questionnaire (IPAQ) and will be completed by interviewers.

#### Inclusion criteria

2.2.4

Eighty patients within the age group of 30 to 50 years of either sex, body mass index (BMI) between 25 and 34.9 kg/m^2^, patients with T2DM who have been diagnosed with at least 2 years history, according to American Diabetes Association criteria, namely fasting serum glucose >7.0 mmol and last HbA1C value >7%, will be recruited from the regional outpatient diabetes care center. The patients should be on the stable doses of oral antidiabetic drugs throughout the study.

#### Exclusion criteria

2.2.5

Having any acute illnesses and presence of some chronic diseases including cardiovascular, kidney, liver, and gastrointestinal diseases and taking related drugs and medications. Any**-**inflammatory and thyroid disease; pregnancy and lactation; menopause; being on insulin regimen; individuals taking drugs such as fibrates (which are PPAR-α ligand) and TZD (which are PPAR-gamma ligand); aspirin, warfarin, and antidepressant medication; history of smoking or alcohol intake at least once a week in the past month; changing diet during the past 3 months; consumption of (at least once a week) ginger or other botanical supplements, antioxidant, and multivitamin/mineral supplement in the past 3 months.

#### Randomization

2.2.6

The participants will be randomly assigned into 2 groups green cardamom powder (n = 40) or rusk powder (n = 40). The permuted block randomization will be used in this study. Stratified randomization will be used to control BMI and gender distribution, those will be 25–29.9/30–34.9 kg/m^2^ for BMI and for gender, respectively. Randomization will be performed by an assistant and the intervention allocation will be blinded as A and B packages for investigators and patients.

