#### Sample size

2.2.2

Eighty patients with T2DM diagnosed by diabetes specialist physicians were recruited from Diabetes Research Center, Endocrinology and Metabolism Clinical Sciences Institute, Tehran University of Medical Sciences Tehran, Iran to detect a significant mean difference of hsCRP,^[28]^ 95% confidence level, and 80% power. Regarding a possible loss to follow-up, a safety margin of 20% was determined The patients were divided equally in the placebo and cardamom supplement groups. We started recruiting participants from Diabetes Research Center from November 20, 2016 to July 20, 2017 and by now we are collecting data from the questionnaires and blood sample tests. 
[figure not shown]

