#### Statistical analysis

2.2.14

The normality of the distribution of data will be assessed by using Shapiro-Wilk tests carried out on each parameter before analysis. By using “regression imputation” missing values will be replaced from a regression equation from observed data. By using intention-to-treat all randomized participants will be analyzed in their group. Independent *t* test will be used to evaluate the differences between the means of 2 independent groups with normal data and Mann-Whitney for non-normal data. In order to assess time-by-treatment interactions and time effects on all outcomes two way repeated-measures regression analysis will be used. A *P* value of <.05 will be considered as significant. All statistical analyses will be performed using SPSS version 21 (SPSS Inc, Chicago, IL).

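### Randomisation is stratified by BMI class and gender but the named tests include neither factor; if either predicts the analysed outcome, the unadjusted test is conservative and forgoes some power

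*Protocol article*

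**What the plan says.** Protocol article, section 2.2.6 (Randomization): "The permuted block randomization will be used in this study", and "Stratified randomization will be used to control BMI and gender distribution". The BMI classes are 25–29.9 and 30–34.9 kg/m². With gender this makes four strata, with 40 patients planned per arm.

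Section 2.2.14 (Statistical analysis) fixes the between-group comparison: an independent t "test will be used to evaluate the differences between the means of 2 independent groups with normal data and Mann-Whitney for non-normal data". It adds a model: "In order to assess time-by-treatment interactions and time effects on all outcomes two way repeated-measures regression analysis will be used". The criterion is a P "value of <.05 will be considered as significant". Neither BMI class nor gender appears in this section, and no adjusted or stratified analysis is mentioned elsewhere in the article.

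Section 2.2.10.1 (Primary outcome) defines the outcomes as changes: blood pressure, NO and ADMA, then the inflammatory and endothelial markers. Section 2.2.2 (Sample size) sizes the trial on hsCRP at "95% confidence level, and 80% power", with a 20% margin for loss to follow-up.

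**The concern.** Blocking within strata balances the arms on BMI class and gender. Variation between strata then largely drops out of the true sampling error of the arm difference. A two-sample test does not know this and still counts that variation as noise. Whenever the strata predict the outcome being analysed, its standard error is too large, its true type I error falls below 5%, and its power is lower than that of a test that includes the factors.

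What is at stake is efficiency. The trial has 80 patients and was planned at 80% power on one marker. The introduction links obesity to higher TNF-α, IL-6 and CRP, so by the protocol's own account BMI class may be related to the level of some of these markers.

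**Working it through.** **Inputs from the article.** Two binary stratification factors, permuted blocks, 40 per arm (2.2.6); significance level 0.05 (2.2.14); 80% power and a 20% margin (2.2.2).

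**Assumptions.** Two-sided test; four equal strata; within-stratum SD of 1; each factor shifts the analysed outcome by s. The article gives no value of s, so a range is shown.

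**The plan's own figure.** The total of 80 cannot be reproduced, because the hsCRP difference and SD come from a cited study and the formula is a figure that is not shown. That is not an error in the plan. It can only be back-solved from d = (1.96 + 0.84) × √(2/n):
- 40 per arm: d = 2.80 × √(2/40) = 0.63.
- 32 per arm (32 / 0.8 = 40 after the margin): d = 2.80 × √(2/32) = 0.70.

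**Step 1: normal approximation, 40 per arm, true difference 0.63.**
- Variance between strata: V = 2 × (s/2)². Share of total variance: R² = V / (1 + V).
- True standard error under balance: √(2/40) = 0.2236. The unadjusted test uses √(1 + V) × 0.2236.
- Its effective critical value is therefore 1.96 × √(1 + V). Type I error = 2 × [1 − Φ(1.96√(1 + V))].
- Standardised signal: 0.63 / 0.2236 = 2.817. Unadjusted power = Φ(2.817 − 1.96√(1 + V)); adjusted power = Φ(2.817 − 1.96) = 80.4%.

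| s | V | R² | √(1+V) | Type I error, unadjusted | Power, unadjusted | Loss (points) |
|---|---|---|---|---|---|---|
| 0.3 | 0.045 | 0.04 | 1.022 | 4.5% | 79.2% | 1.2 |
| 0.5 | 0.125 | 0.11 | 1.061 | 3.8% | 77.0% | 3.4 |
| 0.8 | 0.320 | 0.24 | 1.149 | 2.4% | 71.4% | 9.0 |

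**Step 2: simulation of the same setting** (20,000 balanced trials each; t test against a linear model with both factors, no baseline).

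| s | Type I error, unadjusted / adjusted | Power, unadjusted / adjusted | Loss (points) |
|---|---|---|---|
| 0.3 | 4.8% / 5.2% | 77.8% / 79.3% | 1.5 |
| 0.5 | 3.5% / 4.7% | 75.8% / 79.5% | 3.7 |
| 0.8 | 2.6% / 5.2% | 70.2% / 79.8% | 9.6 |

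**Step 3: a second simulation, scaled to the total SD** (64 evaluable patients, blocks of 4, d = 0.70, 8,000 replicates).

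| R² | Type I error, unadjusted / adjusted | Power, unadjusted / adjusted | Interval width ratio |
|---|---|---|---|
| 0 | 5.0% / 5.0% | 78.5% / 78.4% | 1.00 |
| 0.05 | 4.5% / 5.2% | 78.5% / 80.0% | 1.03 |
| 0.10 | 4.2% / 5.3% | 78.9% / 81.9% | 1.05 |
| 0.20 | 2.9% / 4.8% | 81.6% / 87.7% | 1.12 |
| 0.30 | 2.2% / 5.2% | 82.8% / 91.4% | 1.20 |

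With no stratum effect, adjustment costs essentially nothing. The interval ratio refers to the interval that goes with each test; the article does not itself promise confidence intervals.

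**Step 4: the outcomes as defined, that is, as changes.** If a factor shifts baseline and week 10 equally by s, the shift in the change is s − s = 0. Simulated on change scores with the stratum effect on level only (80 patients, 20,000 trials), power unadjusted against adjusted was 79.5% / 79.5% at 0.3 SD, 79.4% / 79.3% at 0.5 SD and 79.6% / 79.6% at 0.8 SD. Type I error was 4.6–5.2% for both tests. There is no loss.

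**The case against.** The strongest objection is that steps 1 to 3 model a single level, whereas the article defines its outcomes as changes and also tests a time-by-treatment term. A stratum effect on level alone cancels in both, as step 4 shows. This stands. A loss arises only if the strata predict the 10-week change itself, or if week 10 levels are compared. Section 2.2.14 does not say which quantity enters the t test, and the objectives in section 2.1 speak of comparing means, so the second case is not excluded.

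Second, power below 80% for the planned test depends on scaling. In steps 1 and 2 the difference is expressed in within-stratum SDs, so a larger stratum effect inflates the total variance. With 0.63 held in total SDs, unadjusted power was 80.0%, 80.6% and 82.5% at 0.3, 0.5 and 0.8 SD, against about 81%, 84% and 89% adjusted. A reader might infer that the trial falls short of its design power. The documents do not support that: the SD behind the sample size is not readable, and if it is a total SD the planned test keeps its power and merely forgoes a gain.

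Third, nothing in the documents gives an association of BMI class or gender with any outcome, and eligibility narrows the population (BMI 25–34.9, menopause excluded). Shifts of 0.5 to 0.8 SD from both factors on every outcome would be at the high end.

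Fourth, covariates for the repeated-measures regression could be set out in an analysis plan that is not shown. That is fair for the regression. It does not help the t test and the Mann-Whitney, which are named as the between-group tests and carry no covariates.

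**Conclusion.** The mismatch between the stratified design and the named tests is real, and its direction is certain: the unadjusted test is conservative or, at best, unaffected. Its size rests on assumed stratum effects:
- nil if the strata act only on level and changes are compared;
- about 1 to 4 power points if each factor shifts the analysed outcome by 0.3 to 0.5 SD;
- up to about 10 points at 0.8 SD.

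These figures are for a t test against a model with the two factors but no baseline. The Mann-Whitney was not simulated. Once baseline is in the model it already carries part of any stratum effect on level, so the further gain from the strata is likely smaller.

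Two stronger readings are tempting. One is that intervals are too wide and power is lost outright; this holds only if the strata predict the quantity analysed, which the documents neither show nor exclude. The other is that ignoring the strata makes the results invalid; there is no inflation of type I error here, only the reverse. This is an inexpensive improvement in efficiency and in matching the analysis to the design.

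**What to change.** In section 2.2.14, make the main between-group analysis for each outcome a linear model:

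week 10 value ~ arm + baseline value + BMI class + gender

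Transform skewed markers (for example by logarithm) so that the same model serves them in place of the Mann-Whitney. State that the arm coefficient from this model is the main result.

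The cost is one line of text and two degrees of freedom for the strata (four parameters with baseline left out, so 80 − 4 = 76 residual degrees of freedom against 78 for the t test; baseline takes one more). If the strata turn out not to be prognostic, essentially no power is lost. Writing the model down in advance also removes any later choice between adjusted and unadjusted results.

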#### Intervention

2.2.7

The participants will be randomly assigned into 2 groups (green cardamom powder or rusk powder) for 10 weeks. Each patient will receive 2 capsules with each meal (3 g/day) for 10 weeks. Every 5 weeks supplements taken will be checked and empty packs will be received and new packages will be delivered to patients and the number of supplements will be counted. The supplements will be given simultaneously with the usual diabetes care drugs that include maintenance of the oral antidiabetic drugs dosage. All patients receive medical nutrition therapy and physical activity enforcement at this clinic. The 24 hour dietary recall will be taken from all patients at the beginning, middle and end of intervention to be confidant of constant dietary intake. Cardamom and placebo capsules will be prepared by Traditional Medicine Research Center, Tehran, Iran. Each capsule contains 0.5 g of whole green cardamom or rusk powder. Placebo capsules will be completely similar to cardamom capsules by the means of shape, size, and color. All capsules containing placebo will be put on the same bag of the cardamom capsules to take the smell of cardamom. Participants will be asked to keep their usual lifestyle including medical nutrition therapy and physical activity level.

Voucher number of green cardamom is *E cardamomum* (L) Maton, Family: Zingiberaceae, PMP-669 which was identified by School of Pharmacy, Tehran University of Medical Sciences. Essential oil content, essential oil compounds including phenolic and flavonoid content of whole green cardamom using GC-mass and HPLC will be measured in the institute of Medicinal Plants, Shahid Beheshti University of Medical Sciences. Some polyphenolic compounds of green cardamom such as caffeic acid, gallic acid, quercetin, and luteolin, which was mentioned in the other article will be determined by HPLC.^[30]^

#### Adherence

2.2.8

To check patients’ compliance during the 10 weeks, the researcher will interview with them weekly by telephone. In both group (cardamom and placebo), patients will be interviewed to discern whether they are consuming supplements.

#### Patient safety

2.2.9

Patients will be monitored weekly during the study period and all the occurrence of the adverse events will be assessed by patient interview.

#### Study outcomes

2.2.10

##### Primary outcome

2.2.10.1

Primary outcome of this trial includes changes in SBP and DBP, NO, and ADMA. Changes in serum inflammatory markers Il-6, TNF-α, hsCRP, and changes in factors related to endothelial function serum ICAM, VCAM, E-selectin, CD163, and SIRT1.

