##### Secondary outcomes

2.2.10.2

The secondary outcomes of this clinical trial are changes in weight, BMI, and waist circumferences (WCs).

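### Twelve unranked outcomes stand under the primary heading and each is tested at P<.05; if any one suffices, the false-positive chance is about 23–46% (assumed correlations 0.7 to 0), and the stated power covers only hsCRP.

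*Protocol article*

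**What the plan says.** All references are to the protocol article.

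- **Section 2.2.10.1 (Primary outcome)** opens with "Primary outcome of this trial includes changes in SBP and DBP, NO, and ADMA. Changes in serum inflammatory markers Il-6, TNF-α, hsCRP". Under the same heading follow "changes in factors related to endothelial function serum ICAM, VCAM, E-selectin, CD163, and SIRT1". The count is 4 + 3 + 5 = 12.
- **Section 2.2.10.2 (Secondary outcomes)** demotes none of these: "The secondary outcomes of this clinical trial are changes in weight, BMI, and waist circumferences (WCs".
- **Section 2.2.14 (Statistical analysis)** plans a between-group comparison in which a *t* "test will be used to evaluate the differences between the means of 2 independent groups with normal data and Mann-Whitney for non-normal data". A repeated-measures regression is added for all outcomes. The only decision rule is that a *P* "value of <.05 will be considered as significant".
- **Section 2.2.2 (Sample size)** sets 80 patients "to detect a significant mean difference of hsCRP", with 95% confidence, 80% power and a 20% margin for loss.
- **The Introduction** gives the objective as the effect on blood pressure and endothelial function, with inflammatory markers, CD163, SIRT1, NO and ADMA measured to show the mechanism. **Section 2.1 (Objectives)** lists SBP, DBP, NO and ADMA first and hsCRP in the second group.

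**The concern.** A primary outcome tells the reader which single result, or which stated combination of results, decides the trial. Here twelve variables share that status. The text does not say whether one, several or all must succeed, and the threshold of .05 carries no qualification. If one significant result is then read as a positive primary finding, the error rate behind that finding is well above the 5% that the threshold suggests.

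The 80% power belongs to one of the twelve, and that one is not in the group that leads the aim, the objectives or the primary outcome section. The stated power therefore does not describe the question the trial says it asks. The article also presents the study as a base for larger trials, so a chance finding could be carried forward.

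**Working it through.** **1. What can be reproduced.** The plan gives no family-wise error rate; its only error figure is .05. The total of 80 cannot be reproduced, because the hsCRP difference and standard deviation are not in the readable text (a figure is not shown). This is not held against the plan.

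**2. Inputs.** From the article: 12 outcomes (2.2.10.1), alpha .05 per test (2.2.14), 40 per arm (2.2.6). Assumed: two-sided tests; a common correlation ρ between the test statistics; success if any one outcome has P<.05. The article gives neither correlations nor a success rule.

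**3. Any of twelve, either direction, no true effect.** For independent tests the chance is 1 − (1 − .05)^12 = 1 − 0.95^12 = 0.460. For correlated tests, write each statistic as √ρ·U + √(1−ρ)·E, with U a shared standard normal and E independent standard normals. The chance is then 1 − ∫ φ(u)·[Φ((1.96 − √ρ·u)/√(1−ρ)) − Φ((−1.96 − √ρ·u)/√(1−ρ))]^12 du.

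**4. Favourable direction only.** Each test then has a 2.5% chance. For independent tests, 1 − 0.975^12 = 0.262. For correlated tests the lower limit is dropped from the integral, with outcomes oriented so that benefit has the same sign.

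**5. Four outcomes only (SBP, DBP, NO, ADMA), either direction.** For independent tests, 1 − 0.95^4 = 0.185. For correlated tests the exponent is 4 in place of 12.

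| Assumed ρ | 12 outcomes, either direction | 12 outcomes, favouring cardamom | 4 outcomes, either direction |
|---|---|---|---|
| 0 | 46.0% | 26.2% | 18.5% |
| 0.3 | 39.7% | 20.2% | 17.4% |
| 0.5 | 31.9% | 16.0% | 15.6% |
| 0.7 | 23.2% | 11.6% | 13.0% |

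The single-test benchmarks are 5% in either direction and 2.5% in the favourable direction. Simulated two-sided *t* tests with 40 per arm gave 46.3%, 39.9% and 32.3% for twelve outcomes at ρ = 0, 0.3 and 0.5, in agreement with the second column.

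**6. What a correction would cost, as an illustration.** Take an effect that has exactly 80% power at .05. Noncentral-*t* calculations at 32, 33 and 40 per arm put that effect at standardised differences of 0.71, 0.70 and 0.63.

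- At .05/12 = .00417, power is 0.455 to 0.459, about 46%.
- At .05/4 = .0125, power is about 61%.

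These are powers for one outcome at Holm's first, strictest step. They are not powers for the trial.

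**The case against.** **The analysis plan is not shown and may add a correction.** This is fair, and the lack of a named adjustment method is not the point here. What remains is what the article does fix: twelve outcomes under the primary heading, an unqualified .05, and a sample size tied to one of them. A correction elsewhere would have to override this text.

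**A reader might infer that the protocol lets any one result make the trial positive.** It does not say so; it gives no success rule at all. The rates above are therefore conditional on an any-one reading. If all twelve had to succeed, the false-positive rate would not be inflated and the problem would be power.

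**A reader might take 32–46% as the range.** The 32% is only the value at an assumed correlation of 0.5 and is no floor; at 0.7 the rate is 23%. Nor are these rates the chance of falsely claiming benefit, because they include results against cardamom. For benefit alone the range is 12–26%, against 2.5%.

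**The count of twelve could be disputed.** The second sentence of 2.2.10.1 has no verb, and SBP, DBP, NO and ADMA are grouped apart from the rest in the abstract and in 2.1. The heading and the short secondary list favour twelve. With four the rate is still 13–19%, and hsCRP would then not be primary at all.

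**A reader might infer that hsCRP should be the sole primary outcome, since the sample size rests on it.** The documents do not support that. The Introduction gives inflammatory markers a mechanistic role, and the hsCRP inputs cannot be checked. The choice is the sponsor's.

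**Conclusion.** The point stands, and the text should be changed before unblinding. On an any-one reading, the chance of a spurious primary result in either direction is about 23–46% for assumed common correlations of 0.7 to 0. It is 12–26% for results favouring cardamom. If only the first four outcomes are primary, the two-directional rate is 13–19%. All of these exceed the single-test level by a wide margin. They rest on assumed correlations, two-sided tests and an assumed success rule. The within-group comparisons in 2.1 and the repeated-measures model in 2.2.14 would add tests that are not counted here.

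Separately, and without any assumption, the stated 80% power refers to hsCRP while the stated aim leads with blood pressure and endothelial function. The 46% and 61% power figures are illustrations for an effect with exactly 80% power at .05. They should not be entered in the protocol as the trial's power.

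**What to change.** Amend 2.2.10 and 2.2.14 before the A/B allocation code is broken. Recruitment is reported as running to July 2017 and data collection as under way, so the amendment should be dated, disclosed as late, and carried into the registry entry. The sponsor should choose one route:

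- **(a) One primary outcome.** Name it, reconcile it with the aim in the Introduction and 2.1 and with the sample-size outcome in 2.2.2, and make the others secondary and supportive.
- **(b) Several primary outcomes.** List them without ambiguity, specify Holm across them in 2.2.14, and state in 2.2.2 that the 80% power applies to hsCRP at an unadjusted .05 only.

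Either route needs wording changes and no new data. The cost of (a) is that fewer outcomes can be claimed as confirmatory. The cost of (b) is lower power for each outcome.

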##### Secondary outcomes

2.2.10.2

The secondary outcomes of this clinical trial are changes in weight, BMI, and waist circumferences (WCs).

